## Abstract

**Introduction:**

Physical inactivity is the fourth leading risk factor for global mortality, and inactive adults have a higher risk to develop lifestyle diseases. To date, there is preliminary evidence of the efficacy of fitness technologies and other digital interventions for physical activity (PA) promotion. Intervention studies are needed to test the effectiveness and implementation of innovative PA promotion strategies.

**Methods and analysis:**

The ONWARDS study is a hybrid type I effectiveness-implementation randomized control trial aiming at an inactive and presumably high-risk population living in Northern Norway. One hundred and eighty participants will be assigned to 3 groups in a 1:1:1 ratio and participate for 18 months. Participants in group A will be provided an activity tracker with the personalized metric Personal Activity Intelligence (PAI). Participants in group B will be provided with both an activity tracker with the personalized metric PAI and access to online training videos (Les Mills+) to perform home-based training. Participants in group C will be provided an activity tracker with the personalized metric PAI, home-based online training and additional peer support *via* social media. The primary objective is to test which combination of interventions is more effective in increasing PA levels and sustaining long-term exercise adherence. Secondary objectives include: proportion of participants reaching PA recommendations; exercise adherence; physical fitness; cardiovascular risk; quality of life; perceived competence for exercise; self-efficacy; social support; usability; users' perspectives on implementation outcomes (adoption, acceptability, adherence, sustainability). The study design will allow testing the effectiveness of the interventions while gathering information on implementation in a real-world situation.

**Discussion:**

This study can contribute to reduce disparities in PA levels among inactive adults by promoting PA and long-term adherence. Increased PA might, in turn, result in better prevention of lifestyle diseases. Digital interventions delivered at home can become an alternative to training facilities, making PA accessible and feasible for inactive populations and overcoming known barriers to PA. If effective, such interventions could potentially be offered through national health portals to citizens who do not meet the minimum recommendations on PA or prescribed by general practitioners or specialists.

**Trial registration:**

https://clinicaltrials.gov/ct2/show/NCT04526444, Registered 23 April 2021, identifier: NCT04526444.

## Introduction

Physical inactivity is the fourth leading risk factor for global mortality (1). Insufficient physical activity (PA) has major implications for global health and the prevalence of lifestyle diseases, such as cardiovascular conditions, diabetes and cancer, and their associated risk factors (1, 2). Compared to inactive adults, active individuals have lower rates of all-cause mortality, lower risk to develop lifestyle diseases, lower risk of an injury, higher level of cardiorespiratory and muscular fitness, and healthier body mass and composition (3, 4).

According to the WHO 2020 guidelines on PA for health, adults aged 18–64 should perform 150–300 min of moderate-intensity PA per week, or at least 75–150 min of vigorous-intensity PA per week, or an equivalent combination, irrespective of gender, race, ethnicity or income level (5). Worldwide, nearly one third of adults are physically inactive (6). In Norway, only one third of the adult population meets the minimum recommendations on PA (7). In Northern Norway, a region characterized by a high peripherality and adverse weather conditions, PA levels are lower than in Southern Norway (8).

Inactive individuals may not know how, when, where, and with whom they can increase their PA (9). It is especially important to address the key barriers in inactive populations such as psychological factors (lack of motivation, lack of skills/knowledge), environmental obstacles (lack of facilities, bad weather), time constraints (lack of time), and social limitations (lack of social support) (9, 10). Interventions based on behavior change techniques, including goal setting, feedback and monitoring, and social support (11), have been proven to be effective at increasing PA levels in young adults in the shorter-term (12). Further research is needed to determine strategies to achieve longer-term effectiveness of PA interventions (12).

Digital technologies such as wearables, websites and mobile apps are increasingly used in interventions targeting PA together with behavior change techniques and computer-tailored methods (13, 14). Due to their broad availability, digital interventions have the potential to make PA more accessible and feasible for all groups, reduce health inequalities and support long-term adherence to PA recommendations (9, 14).

Consumer-based wearable activity trackers and smartphone apps are now widely available and may offer an alternative method for assisting individuals to remain physically active (9, 15). These devices provide individuals with the ability to objectively monitor their PA levels by features such as distance walked, number of steps, frequency or duration of activity (16) or time spent in various intensities of PA (17). Unlike other PA metrics, heart rate changes reflect the body's response to exercise regardless of the type of activity performed (16). Some apps can also provide tailored feedback through specifically designed algorithms (15). An example is the Personal Activity Intelligence (PAI), which takes into account age, sex and heart rate patterns to provide a single score indicating whether the current PA level is sufficient to obtain or sustain good health (16, 18). Despite representing a promising tool for delivering accessible and appealing PA interventions (19, 20), the evidence supporting the effectiveness of activity trackers and smartphone apps to increase PA is modest at best (15, 21–23). Moreover, there is limited insight into the sustainability of increased PA levels and long-term adherence, and further research should include long-term follow-up assessments (21).

Wearable activity trackers can be used either as the primary component of an intervention or as part of a broader PA intervention (15) which could include other useful components and behavior change techniques. Home-based exercise programs have been shown to be effective in promoting PA in low-active older adults (24). While short-terms effects seem to be achievable, poor adherence to home-based exercise can limit the long-term benefits (25). Home-based online training can provide a platform to scale effective support for sustainable behavior change, thus empowering adults to perform regular PA and increasing engagement over time (20). Participation in home exercise video programmes has been piloted and proven to be feasible (26). Peer support groups represent another well-documented technique to ensure adherence to PA among adults and maintenance of behavior change (27). Peer support provided *via* social media has the potential to support lifestyle change among young adults (28) and further increase the effectiveness of PA interventions and long-term adherence (29, 30). Moreover, the provision of educational information, simple self-monitoring strategies and regular feedback from peers challenging the individuals' capability might help people to maintain PA (31).

This hybrid type I effectiveness-implementation randomized controlled trial (RCT) aims to explore longitudinal changes in PA, long-term exercise maintenance, health and implementation outcomes of an activity tracker with the personalized metric PAI, home-based online training and peer support *via* social media among inactive adults. These digital interventions have the potential to promote PA among high-risk populations, thus resulting in better health and prevention of lifestyle diseases.

## Methods and analysis

### Study design

The ONWARDS study is a hybrid Type I effectiveness-implementation RCT (32) targeting an inactive and presumably high-risk population living in the Troms and Finnmark county in Northern Norway. One hundred and eighty participants will be assigned to 3 groups in a 1:1:1 ratio and participate for 18 months. The effectiveness-implementation hybrid design allows testing the effectiveness of the interventions while gathering information on delivery and potential for implementation in a real-world situation. Participants in group A will be provided with an activity tracker with the personalized metric PAI. Participants in group B will be provided with both an activity tracker with the personalized metric PAI and access to Les Mills+ online workouts to perform home-based training. Participants in group C will be provided with an activity tracker with the personalized metric PAI, Les Mills+ online workouts and additional peer support *via* social media (Figure 1). The presence of three interventional groups will allow testing of which combination of strategies is more effective in increasing PA levels. The study is restricted to participants who volunteer and provide written informed consent in accordance with the Declaration of Helsinki. The trial received approval from the Regional Committee for Medical and Health Research Ethics (66573/REK nord). The protocol of this RCT fulfills the Standard Protocol Items: Recommendations for Interventional Trials (SPIRIT) guidelines (33) and its results will be reported according to the Consolidated Standards of Reporting Trials (CONSORT) statement (34) (Supplementary Table 1).

**Figure 1 F1:**
[figure not shown]
Interventions provided to the three groups.

### Eligibility criteria

To be eligible for enrolment, participants must fulfill the following inclusion criteria: (1) young (18–40 years) or middle aged (40–55 years) healthy adults, both men and women; (2) inactive (undertaking <150 min of moderate-intensity PA per week) in the last 3 months; (3) living in the Troms and Finnmark county; (4) current owner of a smartphone; (5) able to understand training instructions in English language.

Participants will be excluded if they fulfill one or more of the following exclusion criteria: (1) presence of disabilities which might reduce the ability to perform exercise; (2) presence of conditions which might prevent from exercising safely; (3) lack of Internet connection at home; (4) lack of space to exercise safely at home (recommended 4 sqm).

### Randomization and data collection

Randomization will be web-based, stratified by sex, age, and PA level at baseline to obtain homogeneity between study groups. All data collected from the participants will be handled via REDCap (Vanderbilt University, US), a secure web platform specifically geared to support online and offline data capture for research studies. The randomization sequence will be concealed from the study team by the program. Neither study participants nor data analysts will be blinded to group allocation.

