### Outcome measures

The primary outcome is the average time spent in moderate and vigorous PA. Objective measurement of PA will be undertaken using the ActiGraph GT3X+ accelerometer worn at the right hip by each participant for eight consecutive days. The ActiGraph GT3X+ should be taken off when showering or bathing. A day of data will be included if there are at least 10 h of data. A minimum of four valid days of data will be required (36). Total physical activity will be measured as total acceleration counts per minute in triaxal vector magnitude (square root of the summed activity counts from all three axes) counts per minute. The intensity of PA will be split by acceleration cut-off of <150 triaxial counts per minute (sedentary time), 150–2,689 triaxial counts per minute for light and >2,690 triaxial counts per minute for moderate and vigorous PA (37, 38), which are calibrated to correspond to <1.5, 1.5–2.9 and 3.0 metabolic equivalents of tasks (METs).

The proportion of participants reaching the recommendation for PA will be measured, for each group, at all time points (Table 1). Longitudinal changes will express a measure of maintenance of long-term adherence to exercise. The proportion of participants reaching the goal of 100 PAI/week will also be measured for the entire duration of the study.

**Table 1 T1:** Schedule of enrolment, interventions, and assessments.

**Time point**	**Enrolment**	**Baseline**	**6-month**	**12-month**	**18-month**

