### Statistical analysis

Descriptive statistics will be reported as mean and standard deviation for normally distributed continuous variables, or median with interquartile range in the case of skewed distribution. An intention-to-treat analysis will be performed on all randomized subjects to provide unbiased comparisons among groups and avoid the effects of dropout. Study outcomes will be measured as changes from baseline to all assessment points (6-, 12-, 18-month). Changes will be tested with linear mixed models, which account for repeated measures collected in a longitudinal design and deal better with dropouts, without the need for imputation of missing data. Intraclass correlations coefficients will be also reported to take into account the potential correlation among individuals within group. Statistical analyses will be performed with IBM SPSS Statistics.

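### Data analysts are to work unmasked although only participants need to know their arm; the risk is confined to analysis choices still open, and masked labels with a lock would remove it cheaply

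*Protocol article*

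**What the plan says.** In the protocol article, Randomization and data collection states: "Neither study participants nor data analysts will be blinded to group allocation". No reason follows. The sentence before it, "The randomization sequence will be concealed from the study team by the program", concerns how assignments are generated and hidden before allocation. It does not concern who sees the arms during analysis. The article mentions no coded arm labels, no blind data review and no lock of processing before the arms are known.

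Outcome measures defines the endpoint ("The primary outcome is the average time spent in moderate and vigorous PA") and fixes several processing rules: a day counts only with 10 h or more of recording, the number of usable days is set ("A minimum of four valid days of data will be required"), and there is a cut-point of ">2,690 triaxial counts per minute for moderate and vigorous PA". Statistical analysis fixes the model family ("Changes will be tested with linear mixed models, which account for repeated measures collected in a longitudinal design"), an intention-to-treat analysis of everyone randomized, and no imputation of missing data.

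**The concern.** Open delivery explains why participants know their arm: they either have the training platform and the Facebook group or they do not. It does not explain why analysts must know. The article states this as a decision, so it is not a detail that an unseen analysis plan would be expected to supply.

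What is at stake is direction. An analyst who can see which group is which can, without intending to, settle an open choice in the way that favours the expected arm. The trial sets up such an expectation. Study objectives and hypotheses predicts a gain from adding online training and better long-term adherence from adding peer support. Under Peer support via social media, the project team administers and motivates group C's Facebook group. The article does not say whether the same people analyse the data.

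**Working it through.** No figure in the protocol bears on this point, so the check sets the passages side by side.

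**1. Must analysts know the arm in order to produce the primary outcome?** No.
- Every participant wears the same ActiGraph model for eight days at each assessment (Recruitment and study procedures; Outcome measures). It is a separate device from the tracker used in the intervention, so the accelerometer file need not carry the arm.
- All data are handled through REDCap (Randomization and data collection), so group can be recoded on export.
- Allocation is 1:1:1, 180 / 3 = 60 per group, so randomized group size does not give a label away.

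**2. Which choices are fixed, and which does the article's text leave open?**

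| Step | Fixed in the article | Left open in the article |
|---|---|---|
| Valid data | 10 h per day, at least four days | Non-wear definition, epoch |
| Intensity | Counts-per-minute cut-points | – |
| Endpoint | Average time in moderate and vigorous activity | How the average is formed |
| Model | Linear mixed model, change from baseline | Covariates (including the stratification factors sex, age and baseline activity), covariance structure |
| Analysis set | All randomized, no imputation | – |
| Emphasis | 6, 12 and 18 months all analysed | Which time point and which contrast leads |

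On the last row, three groups give three pairwise contrasts (A–B, A–C, B–C). With three follow-up times that makes 3 × 3 = 9 group-by-time comparisons. A full protocol or analysis plan may settle some or all of the right-hand column, and its being open here is not the complaint. The point is that whatever is still open when data arrive would, under the quoted sentence, be decided with arms visible.

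**3. What does masking remove, and what does it not?** For a two-sided test of groups A and B, Z(A,B) = –Z(B,A), so |Z| is the same whatever the groups are called. An analyst who tries several models and keeps the largest |Z| gets the same error rate with labels X/Y/Z as with A/B/C. Masked labels remove only the part of the choice that depends on which named arm benefits. Choice by size of result is removed by locking the code before any result by group is seen. The remedy therefore needs both parts.

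**4. Effect on the design.** Relabelling changes neither the 180 participants nor the power, estimand or visit schedule.

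**The case against.** The case for leaving the sentence alone has force. The choice is openly disclosed, the trial is behavioural and open, and the primary outcome is recorded by a device. Valid-day screening is largely mechanical once the 10 h and four-day rules are set. The model family and analysis set are fixed, and finer modelling detail normally sits in a document not shown. All of this stands, and it is why the risk is described as limited.

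Three stronger readings are tempting, and the documents do not support them.
- A reader might take the sentence on skewed distributions ("or median with interquartile range in the case of skewed distribution") to mean that the primary test may be changed after the data are seen. That sentence governs descriptive summaries only.
- A reader might attach a type I error inflation from picking the best of several analyses. Step 3 of the working shows that such inflation does not depend on masking, so it does not measure this defect.
- A reader might call masked analysis the only protection left in an open trial. Concealed allocation, a device-recorded outcome, preset wear rules and cut-points, intention-to-treat and registration are also in place. Nor would masking analysts mend bias in self-reported secondary outcomes, which arises from participants knowing their arm.

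It can also be said that the cost of masking is not documented. That is correct: the article does not describe staffing. If the people who run the Facebook group also analyse the data, someone must keep the key apart from them.

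None of this supplies a reason for unmasked analysis of the accelerometer outcome.

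**Conclusion.** The point holds in a limited form. The article decides, without a reason, that analysts will see the arms, although nothing in the primary outcome requires it. The exposure is confined to choices not already fixed, and to their being made in favour of an expected arm. Its size cannot be computed from the documents, and no figure should be attached to it.

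The conclusion rests on two assumptions: that some choices will still be open when outcome data become available, and that group can be recoded on export. If an unseen plan fixes every choice before then, little of the risk remains. This is a modest, cheap improvement. It is not a flaw that invalidates the comparison.

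**What to change.** Replace the sentence in Randomization and data collection with:

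> Participants will not be blinded. Accelerometer processing and the primary and secondary effectiveness analyses will use masked group labels (X/Y/Z), with platform-use and Facebook variables excluded from that export. Processing decisions, analysis set and model code will be locked before any outcome results by group are viewed, and labels will be revealed only after the locked analysis has been run.

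If the team finds masking impossible, it should give the reason and fix the open choices before anyone sees outcome data by arm.

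The cost is one recoded variable in the export and an existing team member to hold the key. Analyses of platform use and the interviews, which would reveal the arm, become a separate step. No participants, visits or measurements are added.

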### Description of the interventions

#### Activity tracker With PAI app

Participants in groups A, B and C will be provided with an activity tracker (Mi Smart Band 5, Xiaomi, China) and use the personalized metric PAI through an app (PAI Health, Canada). PAI is a personalized metric based on robust epidemiological evidence which links personalized data to an individual's health (16, 18). PAI takes into account age, sex, resting and maximum heart rate, and analyses a continuous stream of heart rate data acquired from the user to provide a single score indicating whether the current PA level is sufficient to obtain or sustain good health (16). A score of ≥100 weekly PAI has been shown to reduce the risk of premature death due to cardiovascular disease in healthy adults as well as individuals with known risk factors, regardless of whether or not the current PA recommendations were met (18). Moreover, a PAI score ≥100 at baseline, maintaining ≥100 PAIs and an increasing PAI score over time was associated with lower mortality risk (35). Heart rate and accelerometery data are recorded and stored automatically on a daily basis, and an individual feedback on the current PAI score is provided through the smartphone app. This also works as a reminder to keep a weekly PAI score above 100 for disease prevention and health promotion.

All participants will also receive information on recommendations for PA, together with a 6-week acclimatization programme consisting of aerobic activity (two times per week) and muscle-strengthening (one time per week). For aerobic activity, information will be provided on how to exercise in moderate intensity (participants begin to sweat but can speak) including warm up, duration and intensity, examples of activities (e.g., jogging, running, cycling, cross-country skiing, swimming, ball sports, martial arts) and how to make progress in the programme. Participants will be also introduced to high-intensity (hard effort, participants cannot speak) interval training with an example of a 4 × 4 program consisting of four bouts of 4-min high-intensity training and 3-min cool-down. For muscle-strengthening, participants will be provided with an example of programme consisting of five exercises (for legs, back, arms and shoulders) be performed with four sets of four repetitions, and instructed on how to perform each exercise (description and link to a video) and make progress by increasing load.

#### Online training

Participants in groups B and C will have personal access to Les Mills+ (formerly named Les Mills On Demand), an online solution offering videos of training classes available 24/7 *via* a website (https://www.lesmills.com). Workouts include cardio, strength, flexibility, core, and high-intensity training. New releases are available every 3 months to increase motivation, old releases are available to increase variety. Training with other family members or friends at home will be allowed. Les Mills+ is accessible from any device, smart TV with Internet access, pc, laptop, tablet or smartphone.

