### Recruitment and study procedures

Potential participants will be invited primarily *via* Facebook advertised campaigns designed to address adults who fit the inclusion criteria (Figure 2). Advertisement through local newspapers will also be used. People will express their interest, complete an online form including questions on the eligibility criteria (answers will be self-reported), and sign an electronic informed consent. Eligible participants will receive information about the study by e-mail and have a discussion with the research team if needed.

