**Figure 2 F2:**
[figure not shown]
Flow of study participants.

At enrolment, participants will receive the ActiGraph GT3X+ accelerometer by mail, asked to wear it for eight consecutive days and return it by a prepaid mail envelope. Participants will also be asked to measure their waist circumference and complete the online study questionnaires. Participants will then be randomized to one of the three groups and be informed about which group they have been assigned to.

After enrolment, all participants will receive the activity tracker Mi Smart Band 5 directly to their homes and install the PAI Health app on their smartphone. Detailed instructions on how to use the activity tracker and the PAI Health app will be sent to each participant by email, together with together with a 6-week acclimatization programme. Participants in groups B and C will receive personal credentials to access to Les Mills+. Participants in group C will be invited to a Facebook group used for peer support.

At 6-, 12-, and 18-month participants will undergo a follow-up, asked to wear the ActiGraph GT3X+ accelerometer for eight consecutive days, measure their waist circumference, and complete the online study questionnaires. Qualitative interviews will be conducted in a subsample of participants (*n* = 18–20) at 6- and 18-month to explore their perception of the implementation of the interventions. During data collection, participants will be encouraged to continue participating in the study. A gift card (NOK 300) will be sent to each participant after completion of the 6-month follow up to prevent attrition. Data collection for all follow-ups will be performed remotely, as no clinical examinations are planned at any time point. Study end is set 18 months after enrolment.

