### Study objectives and hypotheses

The primary objective of this study is to test which combination of digital interventions is more effective in increasing PA levels among physically inactive adults and sustaining long-term exercise adherence. The secondary objective is to determine the effects on health and implementation outcomes, including: proportion of participants reaching PA recommendations; exercise adherence; physical fitness; cardiovascular risk; quality of life; perceived competence for exercise; self-efficacy; social support; usability; users' perspectives on implementation outcomes (adoption, acceptability, adherence, sustainability).

We hypothesize that the use of activity trackers with the personalized metric PAI can promote PA and improve health outcomes. Furthermore, we hypothesize that the additional use of home-based online training is more effective in engaging in regular PA. Finally, we hypothesize that participation in peer support group *via* social media will result in better long-term adherence to PA.

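### The Les Mills+ permission lets a group A participant train with an enrolled housemate or friend from group B or C, which can dilute the B-versus-A and C-versus-A contrasts

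*Protocol article*

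**What the plan says.** All references are to the protocol article.

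- **Who gets the component.** Under Online training: "Participants in groups B and C will have personal access to Les Mills"+. Study design gives group A the tracker with PAI, group B the tracker plus Les Mills+, and group C both of these plus peer support.
- **Who may join in.** The same section says: "Training with other family members or friends at home will be allowed". It adds that "Les Mills+ is accessible from any device, smart TV with Internet access, pc, laptop, tablet or smartphone", so a second person in the room can follow a class without a log-in.
- **How people are allocated.** Under Randomization and data collection: "Randomization will be web-based, stratified by sex, age, and PA level at baseline to obtain homogeneity between study groups". Recruitment and study procedures confirms that the unit is the individual: "Participants will then be randomized to one of the three groups and be informed about which group they have been assigned to".
- **Who may enrol.** Eligibility criteria lists five inclusion and four exclusion criteria. None concerns a partner, relative, friend or housemate already in the trial.
- **What depends on the contrast.** Under Study objectives and hypotheses: "we hypothesize that the additional use of home-based online training is more effective in engaging in regular PA".

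**The concern.** The second hypothesis can only be tested by comparing group A with groups that have Les Mills+. The permission to train in company is harmless when the companion is outside the trial. When the companion is a group A participant, the comparator receives the tested component, and the text as printed allows it.

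Stratification gives no protection. Household is not a stratum, and a mixed-sex couple falls into different sex strata by construction.

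The direction of the bias is known. Exposed group A members are analysed in group A under the planned intention-to-treat analysis, so any benefit they gain raises the group A mean and narrows B minus A and C minus A. The analysis cannot undo this once the data are collected.

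**Working it through.** **Inputs from the article:** 180 participants, 1:1:1, 60 per group; d = 0.53, power 0.80, alpha 0.05, r = 0.5, attrition 10% (Study design; Sample size).

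**Inputs assumed:** h, the share of participants who enrol with one housemate (no figure is given); full Les Mills+ benefit in every exposed group A member (an upper bound); a two-sided test, since sidedness is not stated.

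**The plan's own figure.** Read as one pairwise comparison of change, r = 0.5 gives SD of change = SD × √(2(1 − 0.5)) = SD, so d stays 0.53.
- n = 2 × (1.960 + 0.842)² / 0.53² = 55.9, so 56 evaluable per group.
- 56/0.9 = 62.2, so 63 per group and 189 in total. Multiplying by 1.1 instead gives 62 per group and 186 in total.
- The stated 180 is close to these but is not reproduced. With 60 × 0.9 = 54 evaluable per group, power is Φ(0.53 × √(54/2) − 1.96) = 78.6%.

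The present point does not depend on this. Sample size refers to longitudinal changes and does not say that 0.53 is the B-versus-A difference, so 0.53 serves below only as an illustration.

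**Chance that a pair is split.** P(one in A, the other in B or C) = 2 × 1/3 × 2/3 = 44%. With fixed group sizes it is 2 × 60 × 120/(180 × 179) = 45%.

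**Share of group A exposed.** c = h × 2/3.

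**Diluted contrast.** d × (1 − c), and power Φ(d(1 − c) × √27 − 1.96).

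| h | People (pairs) | c | Contrast, at worst | Power |
|---|---|---|---|---|
| 0 | 0 | 0 | 0.53 | 78.6% |
| 5% | 9 (4 to 5) | 3.3%, about 2 of 60 | 0.51 | about 76% |
| 20% | 36 (18) | 13.3%, 8 of 60 | 0.46 | about 67% |
| 30% | 54 (27) | 20%, 12 of 60 | 0.42 | about 60% |

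With up to four co-enrolled pairs the power loss stays within about 2.5 points. It passes 5 points only when about 6–7% or more of group A is exposed.

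**Which contrasts are touched.** B minus A shrinks by the fraction c. C minus A loses the same absolute amount, c times the Les Mills+ effect. B versus C is unaffected by this route because both groups hold Les Mills+.

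**The case against.** The strongest reply is that this is a condensed article. Household rules, screening questions and participant instructions may sit in the full protocol or in the e-mails it mentions, and training in company may be a deliberate part of a real-world design. This stands in part: one cannot say that no rule exists anywhere. But the point does not rest on silence alone. The article prints the permission without limit, next to eligibility and stratification lists that leave the route open. The real-world character is kept if companions from outside the trial remain welcome.

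A second reply is that the effect is probably small, and this stands. Both housemates would have to be aged 18–55, inactive for three months, own a smartphone and follow English instructions, among 180 volunteers from a whole county. The group A partner has no log-in and would have to join in regularly to gain the full effect.

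Three stronger readings are tempting and are not supported:

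- A reader might infer that joint sign-up is to be expected because "Potential participants will be invited primarily *via* Facebook advertised campaigns". The article says nothing about couples or friends enrolling together. It is possible, and no more can be said.
- A reader might take the 13–20% exposures as realistic. They need 18 to 27 co-enrolled pairs and full benefit in every exposed member.
- A reader might infer that a group B member living with a group C member receives the peer support. That support is a closed Facebook group to which only group C is invited, and the permission covers training only.

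**Conclusion.** The point holds as a permission drawn too broadly. As printed, a group A member may receive the only component that separates A from B, and the resulting bias runs toward no difference in B versus A and C versus A. Its size is unknown and probably small: at h = 5%, about 3% of group A is exposed and an illustrative 0.53 becomes about 0.51 at worst. This rests on an assumed h, on 2/3 of partners falling in B or C, and on full benefit when exposed. Partial benefit would shrink the effect further. Friends from other households are not counted in h, so the true exposed share could also lie above the housemate figure.

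The documents do not support a claim that this alone would make the online-training hypothesis look null. It is worth correcting because the direction is known, the remedy is simple, and the bias cannot be repaired afterwards.

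**What to change.** 1. In Online training, limit the permission to companions who are not enrolled in another group of the trial. This also covers friends outside the household.
2. Put the same sentence in the instruction e-mail to groups B and C.
3. Accept one participant per household, by adding a question to the existing online eligibility form and a matching line to Eligibility criteria.

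The cost is one question and one sentence, and a few volunteers from shared households are turned away. Training with people outside the trial is unaffected.

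Placing a second household member in the first member's group is not a good substitute. It makes that allocation predictable despite the planned concealment, bypasses the strata and adds household clustering to the analysis.
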